# Continuous intraoperative monitoring of pelvic autonomic nerves during TME to prevent urogenital and anorectal dysfunction in rectal cancer patients (NEUROS): a randomized controlled trial

**DOI:** 10.1186/s12885-016-2348-4

**Published:** 2016-05-21

**Keywords:** Rectal cancer, Autonomic nerves, Intraoperative monitoring, Urinary dysfunction, Sexual dysfunction, Fecal incontinence, Quality of life

## Abstract

**Background:**

Urinary, sexual and anorectal sequelae are frequent after rectal cancer surgery and were found to be related to intraoperative neurogenic impairment. Neuromonitoring methods have been developed to identify and preserve the complex pelvic autonomic nervous system in order to maintain patients’ quality of life. So far no randomized study has been published dealing with the role of neuromonitoring in rectal cancer surgery.

**Methods/design:**

NEUROS is a prospective two-arm randomized controlled multicenter clinical trial comparing the functional outcome in rectal cancer patients undergoing total mesorectal excision (TME) with and without pelvic intraoperative neuromonitoring (pIONM). A total of 188 patients will be included. Primary endpoint is the urinary function measured by the International Prostate Symptom Score. Secondary endpoints consist of sexual, anorectal functional outcome and safety, especially oncologic safety and quality of TME. Sexual function is assessed in females with the Female Sexual Function Index and in males with the International Index of Erectile Function. For evaluation of anorectal function the Wexner-Vaizey score is used. Functional evaluation is scheduled before radiochemotherapy (if applicable), preoperatively (baseline), before hospital discharge, 3 and 6 months after stoma closure and 12 months after surgery. For assessment of safety adverse events, the rates of positive resection margins and quality of mesorectum are documented.

**Discussion:**

This study will provide high quality evidence on the efficacy of pIONM aiming for improvement of functional outcome in rectal cancer patients undergoing TME.

**Trial registration:**

Clinicaltrials.gov: NCT01585727. Registration date is 04/25/2012

## Background

Urinary, sexual and anorectal functional disturbances do frequently occur after total mesorectal excision (TME) for rectal cancer and may tremendously impair patients’ quality of life. In order to reduce the dysfunction rates it is recommended to identify and preserve the pelvic autonomic nerves during the surgical procedure. However, visual nerve identification especially of those located in the minor pelvis (inferior hypogastric plexus, pelvic splanchnic nerves and neurovascular bundles) is challenging due to the complexity of neural distribution and further patient as well as surgery related factors such as a narrow or deep pelvic cavity, the appearance of a voluminous mesorectum, severe obesity, previous pelvic surgery, neoadjuvant chemoradiotherapy, locally advanced tumors with anterior quadrant involvement, supra-anal or juxta-anal tumors, adherence or infiltration of adjacent organs, a bloody situs, use of additional diathermy coagulation and the applied dissection techniques [1–4]. Therefore, poor nerve visualization and lack of neuroanatomical knowledge will consequently result in inadvertent nerve damage.

Pelvic intraoperative neuromonitoring (pIONM) was introduced to rectal cancer surgery to serve as a novel method for improvement of nerve identification and further verification of its functional integrity. In previous investigations it could be already shown that the electrophysiological nerve identification is superior to sole visual assessment [5]. A recently developed pIONM method is based on electric stimulations of pelvic autonomic nerves under simultaneous observation of processed electromyography (EMG) of the internal anal sphincter (IAS) and manometry of the urinary bladder. Its suitability for accurate assessment of nerve function and its predictive potential of functional outcome has been demonstrated by previous non-randomized single-center studies [6, 7]. In a recent case-control study pIONM controlled TME in rectal cancer patients was found to offer better functional outcome compared to patients undergoing surgery without the use of this method [8]. An actual retrospective investigation supports these findings by demonstrating superior urogenital function in patients undergoing rectal cancer surgery with electrophysiological control [9]. The results are encouraging. However, high quality evidence on the efficacy of pIONM is missing. In order to close the gap, we are conducting the first randomized multicenter trial comparing urogenital and anorectal functional outcome in rectal cancer patients undergoing TME with or without pIONM.

## Methods/design

### Objectives

The primary objective of this trial is to assess urinary functional outcome in rectal cancer patients undergoing TME with pIONM, when compared to TME without pIONM, in a 12 months follow-up period per patient. The secondary objectives are to assess sexual and anorectal functional outcome in rectal cancer patients undergoing TME with pIONM, when compared to TME without pIONM, in a 12 months follow-up period per patient and to assess the safety, especially oncologic safety and quality of TME.

### Trial design

The NEUROS study is a prospective two-arm randomized controlled multicenter clinical trial with a follow-up period of 12 months per patient.

### Study population

Patients undergoing TME for rectal cancer presenting at one of the participating hospitals.

#### Inclusion criteria

Histologically confirmed rectal cancer (≤ 16 cm from anal verge)Suitable for radical surgeryTMEAge 18-90 yearsInformed consent

#### Exclusion criteria

Emergency operationPacemakerMultivisceral resectionPartial mesorectal excisionTransanal endoscopic microsurgeryOngoing infection or sepsisSevere untreated physical or mental impairmentPregnancy or breastfeedingWomen of childbearing potential who are not using a highly effective birth control methodMissing preoperative data on urogenital or anorectal functionSimultaneous participation in another clinical trialPrevious participation in this clinical trialLack of compliance with the trial procedure

### Outcome measures

Assessment of urinary function is carried out on the basis of the International Prostate Symptom Score (IPSS, total score range from 0 to 35 points) and the Quality of life index (Qol, Quality of life due to urinary symptoms, total score range from 0 to 6 points) [10]. A higher score indicates diminished urinary function and quality of life. Previous studies reported that the IPSS also applies to females and demonstrated that women have comparable scores to those of age-matched men [11, 12].

Sexual function in females is evaluated with the Female Sexual Function Index (FSFI) and in males with the International Index of Erectile Function (IIEF). The FSFI has been developed and validated as a brief, multidimensional self-report instrument for assessing the key dimensions of sexual function in women. It was designed and validated for assessment of female sexual function and quality of life in clinical trials and has demonstrated ability to discriminate between clinical and non-clinical populations [13]. The FSFI is a 19-item questionnaire with a total score range from 2 to 36 points. A lower score indicates diminished sexual function. The IIEF has been developed and validated as a brief and reliable self-administered scale for assessing erectile function [14]. The IIEF is a 19-item questionnaire with a total score range from 5 to 75 points. The brevity and ease of comprehension of the measure provide practical advantages.

Anorectal function is determined by the Wexner-Vaizey score (WVS) (minimum score = 0 = perfect continence; maximum score = 24 = totally incontinent) [15].

### Sample size calculation

The rate of patients with an IPSS increased by at least 5 points 12 months after surgery compared to the preoperative IPSS is assumed to be 10 % in patients undergoing TME with pIONM. The corresponding rate for patients undergoing TME without pIONM is expected to be 30 %. A total number of 164 study patients is needed to demonstrate a significant difference between the study arms with a power of 90 % using Fisher’s exact test (alpha = 0.05, two-sided). Dropout rates are expected to be 2 % perioperatively and 10 % during the follow-up period in both study arms resulting in an overall dropout rate of 12 %. 188 patients have to be allocated to the trial.

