### Endpoints

#### Primary endpoint

Primary endpoint is the increase of the IPSS by at least 5 points observed 12 months after surgery compared to the preoperative IPSS per patient. In case of postoperative urologic treatment for newly developed urinary dysfunction, primary endpoint is the increase of the IPSS by at least 5 points observed before urologic treatment compared to the preoperative IPSS. The primary endpoint is based on previous findings [16]. In a group of 61 patients undergoing mesorectal excision for rectal cancer we observed long-term urinary deterioration in 13 patients determined by the IPSS. The median difference in the IPSS was 6 points (range: 1-25 points, interquartile range: 4-8 points). Answers to additional questions on the Qol ranged from 0 (delighted) to 6 (terrible). We found that an increase of the IPSS by at least 5 points leads to a clear decrease in patients’ quality of life due to urinary symptoms (median difference in the Qol score was 3 points (interquartile range: 2-4 points)).

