### Randomization and blinding

All patients who meet the inclusion criteria will be randomized. Randomization ratio is 1:1 to TME with pIONM or TME without pIONM (Fig. 1). Randomization is stratified according to neoadjuvant therapy and gender using blocks of variable length. Central randomization via FAX is conducted in this study.

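### The 30% control rate behind the sample size has no stated source and is not reconciled with the article's own cohort, which suggests a lower rate and power below 90%

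*Protocol article*

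**What the plan says.** The Sample size calculation section defines the event as an IPSS rise of at least 5 points from the preoperative value at 12 months. The event rate "is assumed to be 10 % in patients undergoing TME with pIONM", and for the control arm "The corresponding rate for patients undergoing TME without pIONM is expected to be 30" %. From these, "A total number of 164 study patients is needed to demonstrate a significant difference between the study arms" "with a power of 90" % by Fisher's exact test ("alpha = 0.05, two-sided"). Allocation is 1:1 (Randomization and blinding). No reference or data are attached to either rate.

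The Primary endpoint section describes an earlier group of 61 patients who had mesorectal excision for rectal cancer: "we observed long-term urinary deterioration in 13 patients determined by the IPSS". It continues: "The median difference in the IPSS was 6 points (range: 1-25 points, interquartile range: 4-8 points". These patients are used there to justify the 5-point threshold through its effect on urinary quality of life. The article gives no other IPSS event rate for surgery without pIONM.

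**The concern.** The trial counts only rises of 5 points or more. The cohort's 21.3% counts any long-term deterioration, down to 1 point, and is already below 30%. The rate for the trial's own event must be lower still, because the 13 include patients with rises under 5 points. So the article gives two figures for much the same quantity, about a factor of two or more apart, and does not comment on the gap.

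The power statement rests on the higher figure. If the true control rate is nearer the cohort's, there are fewer events, the absolute difference shrinks, and a real benefit is more likely to be missed. A non-significant result could then be read as absence of benefit by readers relying on the stated 90%.

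**Working it through.** **Inputs.** From Sample size calculation: 10% v 30%, 164 evaluable patients, two-sided alpha 0.05, power 90%, Fisher's exact test. From Randomization and blinding: 1:1, so 82 per arm. From Primary endpoint: 13 of 61 deteriorated, median 6, range 1-25, IQR 4-8. I take the median and quartiles to describe the 13 who deteriorated, which is how the text reads.

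**Step 1: reproduce the plan's figure.** The normal-approximation formula without continuity correction, with mean rate 0.20, is

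n per arm = [1.960·√(2·0.20·0.80) + 1.282·√(0.10·0.90 + 0.30·0.70)]² / (0.30 − 0.10)² = (1.109 + 0.702)² / 0.04 ≈ 82.

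Twice 82 is 164, so the stated total reproduces as a chi-square figure. Exact enumeration of Fisher's two-sided test at 82 per arm gives 87.1%. This is the starting point for the comparisons below.

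**Step 2: the cohort's rate for the trial's event.**
- Any deterioration: 13/61 = 21.3%.
- With 13 ordered whole-number values, the median is the 7th. It is 6, so the 7th to 13th values are all at least 6, and at least 7 patients rose by 5 or more.
- If the lower quartile is the 4th value, four values are at most 4, which leaves at most 9 at 5 or more. If it is the average of the 3rd and 4th values (for example 3 and 5), it allows 10. Enumeration under 12 quartile definitions gives 7 to 9 under eight of them and 7 to 10 under four.
- The rate is therefore 7/61 = 11.5% to 10/61 = 16.4%.

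**Step 3: sampling uncertainty (Clopper-Pearson 95% upper limits, all 61 as denominator).**

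| Count | Rate | Upper limit |
|---|---|---|
| 7/61 | 11.5% | 22.2% |
| 9/61 | 14.8% | 26.2% |
| 10/61 | 16.4% | 28.1% |
| 13/61 (any rise) | 21.3% | 33.7% |

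**Step 4: power of Fisher's exact test at 82 per arm, by enumeration.** The first power column keeps the planned risk ratio (10/30 = one third). The second holds the pIONM rate at 10%, which makes the assumed benefit smaller as the control rate falls.

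| Control rate | Power, risk ratio 1/3 | Power, pIONM fixed at 10% |
|---|---|---|
| 30% | 87% | 87% |
| 25% | 78% | 66% |
| 21.3% | 69% | 44% |
| 16.4% | 55% | 17% |
| 14.8% | 49% | 11% |
| 11.5% | 35% | 4% |

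The 25% row is illustrative; the lower rows come from the cohort.

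**The case against.** A reader might infer that the cohort contradicts 30%, since even 10/61 has an upper limit of 28.1%. The documents do not support that, for four reasons.

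- **Source.** The article never says that the 30% came from these 61 patients; it uses them to justify the threshold. The Background cites two comparative studies of functional outcome with and without electrophysiological control, and the full protocol may hold a derivation. Neither can be seen here.
- **Population.** The cohort had mesorectal excision, whereas the trial excludes partial mesorectal excision. The split is not given. As an assumption, if all 10 events fell among 55 TME patients, the exact upper limit would be 30.9%; for 10 of 50 it would be 33.7%. With 7 events a smaller subset is needed: 7/45 has a limit of 29.5% and 7/40 one of 32.8%. The exclusion of 30% is therefore fragile.
- **Endpoint.** The trial carries earlier postoperative scores forward when month 12 is missing and uses the last score before urologic treatment. Both rules may raise the event rate above a long-term deterioration rate. The cohort's exact time point, its handling of treated patients and any use of pIONM are not stated.
- **Consequence.** It is also tempting to say that the trial could not show a benefit. Power of 35% to 69% at the planned risk ratio does not support this, and the lowest figures in Step 4 assume a smaller benefit than the one planned.

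All four limit the claim. None supplies a basis for 30% or explains the gap from 13/61, and the article states no allowance for any of them. The point is not merely something left to the analysis plan, because both figures stand in this article.

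**Conclusion.** The point holds as a matter of unsupported and apparently optimistic planning. The 30% is unsourced and is not reconciled with the only event data in the article, which give 21.3% for any deterioration and 11.5% to 16.4% for the trial's event. The cohort does not show that 30% is wrong for TME-only patients.

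Over control rates from 25% down to 11.5%, power with the planned risk ratio kept runs from about 78% to 35%. It may therefore be substantially below 90%; even the planned rates give 87% with the named test. These figures assume 82 evaluable patients per arm, Fisher's exact test, a constant risk ratio of one third, and quartiles that describe the 13 deteriorated patients.

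**What to change.** 1. Give the source for 30% and reconcile it with 13/61, saying how the populations, time points and scoring rules differ. Alternatively, replace the single 90% with exact Fisher power over control rates of about 12% to 30%, and say whether the risk ratio or the pIONM rate is held constant.
2. State that a non-significant result will be interpreted through the 95% confidence interval of the risk difference.
3. Optionally, add a supportive comparison of 12-month IPSS adjusted for preoperative IPSS and the stratification factors (neoadjuvant therapy and gender). It uses data already collected, but does not itself settle whether 30% is justified.

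The cost is wording, a short table and, if item 3 is taken up, one regression. No patients are added. The drawback is that the stated power becomes less favourable.

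### 164 evaluable patients give 87.1% power, not 90%, with the two-sided Fisher's exact test that the sample size section names

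*Protocol article*

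**What the plan says.** The section "Sample size calculation" of the protocol article gives every input that the power claim needs:

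- The event is a rise in IPSS of at least 5 points at 12 months. Its rate "is assumed to be 10 % in patients undergoing TME with pIONM".
- For the control arm: "The corresponding rate for patients undergoing TME without pIONM is expected to be 30" %.
- Number and power: "A total number of 164 study patients is needed to demonstrate a significant difference between the study arms with a power of 90" %.
- Test: "using Fisher’s exact test (alpha = 0.05, two-sided").
- Losses of 2% perioperatively and 10% in follow-up, "resulting in an overall dropout rate of 12" %, after which "188 patients have to be allocated to the trial".

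The section "Randomization and blinding" adds: "Randomization ratio is 1:1 to TME with pIONM or TME without pIONM". The 164 evaluable patients are therefore meant as 82 per arm.

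**The concern.** Fisher's exact test is conservative in samples of this size, so it needs more patients than the chi-square test for the same nominal power. A total of 164 for 10% against 30% looks like the chi-square figure. If so, the plan reports the power of one test under the name of another, and its real chance of missing the assumed effect is higher than the 10% stated. The choice of test then matters, because Fisher's test and the chi-square test fall on opposite sides of the 90% target on the same 164 patients.

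**Working it through.** **Inputs.** p1 = 0.10, p2 = 0.30, mean 0.20, difference 0.20, two-sided alpha 0.05 (z = 1.960), power 0.90 (z = 1.2816), 1:1 allocation. All come from the two sections cited above.

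**Step 1: reproduce 164.** The pooled normal approximation without continuity correction is

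n per arm = [1.960 × √(2 × 0.20 × 0.80) + 1.2816 × √(0.10 × 0.90 + 0.30 × 0.70)]² / 0.20²

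= (1.1087 + 0.7019)² / 0.04 = 81.96, rounded up to 82 per arm, **164 in total**.

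This matches the plan exactly. Other formulas do not: the unpooled and arcsine versions each give 79 per arm, and the continuity-corrected version gives 91.69, so 92 per arm (184 in total). The correction is commonly used to approximate Fisher's test.

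**Step 2: power of the named test.** The power of Fisher's test at n per arm is the sum of Bin(x; n, 0.10) × Bin(y; n, 0.30) over all pairs (x, y) with a two-sided Fisher p-value of at most 0.05. Full enumeration gives:

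| Per arm | Total | Fisher, two-sided | Pearson chi-square |
|---|---|---|---|
| 82 | 164 | **87.1%** | 91.1% |
| 88 | 176 | 89.8% | 92.7% |
| 89 | 178 | 90.2% | 92.9% |
| 92 | 184 | 91.3% | 93.7% |

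With equal arms, the two usual definitions of the two-sided Fisher p-value (probability-ordered and doubled tail) give the same power.

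**Step 3: actual size of the tests at 82 per arm.** At a common event rate of 20%, Fisher's test rejects about 3.1% of the time. The uncorrected chi-square test rejects at most about 5.1% of the time over all common rates.

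**Step 4: unequal splits of 164.** Every split from 76/88 to 89/75 (with/without neuromonitoring) was enumerated. Probability-ordered Fisher gives 87.1% to 89.9%, and doubled-tail Fisher gives 86.5% to 87.7%. No split reaches 90%.

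**Step 5: dropout.** 164 / 0.88 = 186.4, so 187, and 188 as the next even number. That inflation is consistent. In the other direction, 188 × 0.88 = 165.4 evaluable. On the same basis, 178 evaluable would need 178 / 0.88 = 202.3, so 203 randomised.

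**The case against.** Four points can be made for the plan.

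1. **Exact balance is the unfavourable case.** At 82/82 the probability-ordered Fisher test is at its most conservative; 83/81 gives 89.8% and 80/84 gives 89.9%. At 165 evaluable, 83 with and 82 without neuromonitoring gives 90.1%. Averaged over 94 randomised per arm with independent 12% losses (an assumption), power is 89.2%. This stands as a limit on the size of the problem, but it does not rescue the claim. The reverse split at 165 gives 88.1%, so the 90.1% is an effect of discreteness. The doubled-tail version stays at about 87% to 88%.

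2. **More than 164 may be analysed.** The section "Statistical analysis" excludes only patients without any postoperative IPSS and carries the last score forward for the others. If only the 2% perioperative losses drop out, about 184 are analysed (188 × 0.98) and Fisher's power is about 91.3%, provided that carried-forward scores show the same 10% and 30% rates. The trial may therefore reach 90% in practice. But the sample size section deducts the full 12% and does not use this argument.

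3. **The origin of 164 is inferred.** This is correct. The article names no formula or software. The power of Fisher's test at 82 per arm does not depend on where the number came from.

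4. **No conclusion is put at risk.** Fisher's test keeps its type I error below 5%, and a gap of up to 3 points is small beside the uncertainty in the assumed rates. This is fair and bears on priority. A stated power that the named test does not have should still be corrected.

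**Conclusion.** The concern holds. For the rates, alpha, sidedness and test that the article states, 82 per arm gives 87.1% power, 2.9 points below the claim. Type II error is 12.9%, about 30% higher in relative terms than the stated 10%. With equal arms, 90% is first reached at 178 evaluable patients, 14 more than planned (8.5%).

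The figure of 87.1% rests on exactly equal arms and on 164 patients analysed. Unequal splits of 164 reduce the gap under the probability-ordered definition without closing it. Retaining dropouts by carrying scores forward could close it in the trial as run. The error is certain as a statement about the named test, modest in size, and no threat to the validity of the result.

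**What to change.** Make the named test and the stated power agree, in one of two ways:

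- **Name the uncorrected Pearson chi-square test as the primary test.** The 164 patients then stand, with about 91% power at 82 per arm and a type I error of at most about 5.1% at that split. A Cochran–Mantel–Haenszel test over the randomisation strata (neoadjuvant therapy and gender) would be a natural alternative, but its power was not calculated here and should be confirmed before it is named.
- **Keep Fisher's exact test and state the power as about 87% at 164 evaluable patients.** If the sponsor expects carried-forward scores to raise the number analysed, say so and give the power at that number with the assumption behind it.

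Either way, carry the choice through to the section "Statistical analysis". That section names the Wilcoxon signed rank test for comparing the rates, which matches neither Fisher's test nor the arithmetic that yields 164.

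The cost is wording only, with no extra patients. The choice should be fixed before the database is closed and unblinded.
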